### Statistics

Non-inferiority will be considered to have been confirmed if the lower bound of the 95 % two-sided confidence interval for the difference between the occurrence

| Factor                                                                                                                     |                         | Points | Red             | Orange           | Yellow               | Green         |
|----------------------------------------------------------------------------------------------------------------------------|-------------------------|--------|-----------------|------------------|----------------------|---------------|
| Oxygen treatment                                                                                                           | +                       | 4      | 8-14 points     | 4-7 points       | 2-3 points           | 0 points      |
| Systolic blood pressure                                                                                                    | < 100 mmHg              | 3      | Resuscitation   | Emergent         | Urgent               | Non-urgent    |
| Respiratory rate                                                                                                           | > 22 min   | 3      | Life threatened | Critical illness | Potentially unstable | Stable        |
| Heart rate                                                                                                                 | > 110 min  | 2      | Constant        | Re-evaluation    | Re-evaluation        | Re-evaluation |
| SpO 2                                                                                                           | < 94 %                  | 2      | Re-evaluation   | Every 15 min     | Every 60 min         | Every 180 min |
| A clinical assessment on arrival:                                                                                          |                         |        |                 |                  |                      |               |
| Triage nurse can move the patient one triage level down or up to two levels up based on his/her own evaluation of symptoms |                         |        |                 |                  |                      |               |

Red

Orange

Yellow

Green

**Fig. 1** The Copenhagen Triage Algorithm

**Fig. 1** The Copenhagen Triage Algorithm

**Table 2** Results of the multiple logistic regression using the CTA cut-off values on the TRIAGE database

|                       | Odds ratio | p |
|-----------------------|------------|----------|
| Oxygen treatment      | 4,27       | <0,01    |
| Systolic BP < 100     | 3,28       | <0,01    |
| Heart rate > 110      | 2,14       | <0,01    |
| Respiratory rate > 22 | 2,71       | <0,01    |
| SpO2 < 94 %           | 1,67       | <0,01    |

of the primary endpoint in the CTA and DEPT cohorts does not include  $-\Delta$ . Furthermore, CTA could show superiority over DEPT; this will be considered when the lower bound of the confidence interval mentioned above exceeds 0. This analysis will only be performed if non-inferiority is confirmed. The power to demonstrate that CTA is superior will be 0.72 with a sample size of 40.000, while there will be a 5 % chance that DEPT triage is better. LOS and time-to-treatment in the two models will be log-transformed and compared using parametric tests. The patient populations included with CTA and DEPT will be compared using standard parametric tests.

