### Sample size

The trial is designed as a non-inferiority trial, i.e. to show that 30-day mortality using CTA is not higher than using DEPT. The 30-day mortality in all admitted patients in the TRIAGE database was 4.2 % [24] and the 28-day mortality in the Acute Admission Database was 4.2 % [28]. Hence, we estimated the 30-day mortality to be 4.2 % for this study. Due to the estimated low incidence of the primary end-point, the proportional difference between the CTA and DEPT group (non-inferiority margin ( $\Delta$ )) is set at 0.5 %. The power to confirm non-inferiority is set at 80 % with a two-sided confidence interval of 95 %, which would require a sample size of 39,820. We chose to include a minimum of 40,000 patients. The combined percentage of admission to intensive or semi-intensive care unit in the TRIAGE database was 3.4 % [24], i.e. sample size should be adequate to prove non-inferiority for this secondary end-point as well. Reported 30-day readmission rate is usually around 10 % [29] meaning sample size will likely be sufficient to prove non-inferiority. In calculating the primary end-point of 30-day mortality, patients readmitted more than 30 days after discharge will be considered as separate encounters.

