### Discussion

Emergency department (ED) triage impacts most patients and it can be a valuable tool for managing a crowded and busy ED. However, existing models of triage are supported by limited evidence. The Copenhagen Triage Algorithm (CTA) aims to be a faster and better way to identify acutely ill patients as well as the less urgent patients in the ED. The CTA Study is a randomized trial comparing CTA to the standard Danish Emergency Process Triage (DEPT) in an unselected population. To the best of our knowledge, this is the first study to prospectively evaluate a triage model in a randomized study. If the hypothesis of non-inferiority in detecting mortality is confirmed CTA will provide less resource consuming method of triage in the ED while still identifying patients in need of urgent care.

The time and resources used on systematic triage is not without a price as crowding in the ED is a well-established risk that can compromise patient safety [1]. Overcrowding in the ED happens when the patient load exceeds the available resources. This situation leads to increased length of stay and mortality across patients both high and low risk [30, 31]. A retrospective study of visits to the Canberra Hospital ED [31] showed that patients presenting to the ED during “overcrowded shifts” had a 34 % higher risk of 10-day in hospital mortality than patients presenting during normal shifts. This risk persisted even when accounting for level of triage (by Australasian Triage Scale) suggesting a level of under-triage during crowded shifts [31]. A systematic review of crowding in the ED [30] found ED bottlenecks to be common in the literature often arising from inadequate staffing. As triage by definition is time and resource consuming, speeding up this process alone could help alleviate some of these problems.

Compared to other triage models CTA is a vastly simpler model comprised of vital signs (blood pressure, heart rate, arterial oxygen saturation, respiratory rate, and the need for oxygen treatment) combined with a clinical assessment by the ED nurse. Since vital signs are measured as part of any patient admission except for minor injuries, the only additional time consuming part

[figure not shown]

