of CTA is the clinical assessment which can be done in few minutes even by clinically uneducated staff [25]. This is contrasted by most existing triage models such as ATS, MTS, DEPT and CTAS that use extensive lists of primary complaint or causes of contact [14, 21] aimed at identifying potentially urgent patients. These aim to find the patients primary symptom and triage based on prior consensus of the urgency of symptoms. These are mostly based on expert opinion and has been shown to lead to over-triage, increasing the triage level for about half the patients while lowering the sensitivity and specificity of the final triage [21].

Abnormal vital signs are strong predictors of mortality in patients admitted through ED's [21]. Though smaller studies have shown that vital signs alone are insufficient to detect the critically ill [32, 33], combining these with a clinical assessment by the ED nurse may significantly improve this without using extra resources [25]. Which vital signs and cut-off points should be used is still a subject of debate. In most models, like the ATS, it is established by expert opinion [34] and a systematic review of the literature from 2011 by Farrohknia et al. [15] showed limited or insufficient evidence for any of the vital signs usually used in triage models (respiratory rate, arterial oxygen saturation, heart rate, and level of consciousness). Thus we decided to define new cut-off values based on the large cohort of patients we had gathered.

As the vital signs were meant to reflect acute illness, we chose not to include age as a factor in the score. Biomarkers were not a part of this study though several biomarkers have been shown to be strong predictors of mortality [35, 36]. In the future, a combined score of vital signs and biomarkers may be the most sensitive method of detecting the vast amount of non-urgent patients visiting the hospital every day [24, 37].

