### Limitations

The primary end-point is 30-day mortality which is associated with multiple factors besides the triage model used at admission. Mortality has been used previously to assess the efficacy of triage models [19, 21–23]. If CTA has any impact on acute mortality (e.g. 8 h) it would also affect 30-day mortality given it is the only intervention performed. However, if 8-h mortality was chosen as primary end-point, it would favor a model ranking a majority of patients in acute category and not necessarily reflect the impact on less acute patients who might die during hospitalization or within the first month. Admission to ICU as secondary endpoint was chosen to reflect a more immediate impact of triage.

In the acute care setting, it is not feasible to randomize individual patients for different triage models for several reasons. The individual randomization would be a huge logistical challenge in a busy ED and it would be

associated with delays and crowding, which would be unethical. Furthermore, it is likely that the staff would prefer the faster algorithm (CTA) and tend to use that in most patients once it is available in the department. To avoid this, cluster-randomization was chosen. Cluster-randomized design introduces dependence between individual units sampled (e.g. difference in patient population, skill of ED nurses/physicians). This is largely alleviated by cross-over in the study and relies on a similar patient inclusion during both parts of the study. This is ensured by determining the total study period through number of included patients instead of time. Furthermore, the number of clusters were very small but the cross-over design partly compensates for this.

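### The protocol handles case-mix only by testing the two populations and names no covariate for the primary mortality difference, so case-mix change that differs by hospital and period would pass into the non-inferiority verdict

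*Protocol*

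**What the plan says.** The Statistics section rests the verdict on the two-sided 95 % confidence interval for the difference in the occurrence "of the primary endpoint in the CTA and DEPT cohorts". It names no covariate, hospital or period term. On patient mix it says only: "The patient populations included with CTA and DEPT will be compared using standard parametric tests". Nothing is said to follow from the result.

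The Limitations section lists differences in patient population among the sources of dependence in a cluster design. It says the cross-over largely deals with them, and that this "relies on a similar patient inclusion during both parts of the study". It treats that similarity as secured by fixing the study length by patient numbers rather than by time.

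The Sample size section sets the margin at 0.5 points: "Hence, we estimated the 30-day mortality to be 4.2 % for this study". Table 2 gives the odds ratios for 30-day mortality: oxygen treatment 4.27, systolic pressure 3.28, respiratory rate 2.71, heart rate 2.14, saturation 1.67. The Discussion indicates that these signs are available for most patients: "Since vital signs are measured as part of any patient admission except for minor injuries".

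**The concern.** Two hospitals over two periods were allocated, not patients, so randomisation cannot be relied on to balance age or severity. Equal patient counts do not make patients equally ill. The periods also cover different parts of the year (1 March to 17 August 2015, then to the end of January 2016, under Timeline).

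A significance test answers the wrong question here. It depends on sample size and not on what an imbalance does to mortality, and it leaves the estimate unchanged whatever it shows. Because the margin is small beside the outcome's dependence on severity, a residual imbalance can push the verdict either way: towards accepting a worse triage model, or towards failing an equally good one.

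**Working it through.** **1. The plan's own figure and the resulting precision.** Inputs from Sample size: mortality 4.2 %, margin 0.5 points, 80 % power, two-sided 95 % interval. Per arm, n = (z(1−α) + z(0.80))² × 2p(1−p)/Δ².
- α = 0.025 one-sided, which is what a two-sided 95 % interval implies: 7.849 × 0.080472/0.000025 = 25,265 per arm, 50,530 in total.
- α = 0.05 one-sided: 6.183 × 3,218.9 = 19,901 per arm, 39,802 in total.

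The plan's figure ("which would require a sample size of 39,820") is therefore reproduced closely only at one-sided 5 %. That is a separate point. Here it explains the baseline power: about 70 % at 20,000 per arm, and about 80 % at 25,000 per arm (the roughly 50,000 visits recorded, split 1:1). The standard error at 25,000 per arm is √(0.080472/25,000) = 0.179 points. All figures treat visits as independent.

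**2. What the cross-over cancels.** Call the hospitals A (CTA first) and B (DEPT first), with equal numbers in each cell. The case-mix part of CTA minus DEPT is then [(A1 − A2) − (B1 − B2)]/2. A constant difference between A and B drops out, and so does a period shift common to both. A change over time that differs between the hospitals remains. If sizes follow the stated 70,000 and 85,000 annual admissions, a fraction (85 − 70)/155 = 0.097 of a common seasonal difference also remains. An assumed seasonal difference of 0.5-1.0 points in mortality leaves 0.05-0.10 points, or none with equal recruitment.

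**3. How far a residual imbalance moves mortality.** Model: logit(risk) = a + Σ xⱼ ln(ORⱼ) with the Table 2 odds ratios, over all 32 combinations of independent factors, with a solved so that overall mortality is 4.2 %. The 10 % cut-off rule in the Copenhagen Triage Algorithm section suggests a prevalence near 10 % for the vital signs. For oxygen treatment none is given. I assume a range of 5-15 % for all five. One arm's prevalence is then raised by 1 percentage point.

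| Shift in mortality (points) | 5 % | 10 % | 15 % |
|---|---|---|---|
| Oxygen treatment alone | 0.100 | 0.089 | 0.080 |
| All five factors together | 0.302 | 0.275 | 0.254 |

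One-factor check for oxygen at 10 %: risk is 3.27 % without and 12.60 % with, so a 1-point imbalance gives 0.01 × 9.33 = 0.093 points. The weaker factors at 10 % give 0.067 (systolic pressure), 0.053 (respiratory rate), 0.038 (heart rate) and 0.023 (saturation).

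**4. Effect on the verdict at 25,000 per arm.** For a shift b in CTA's favour when CTA is truly 0.5 points worse, false non-inferiority = Φ(b/SE − 1.96), with SE = √[(0.042×0.958 + 0.047×0.953)/25,000] = 0.184 points. For a shift b against CTA when mortality is equal, power = Φ((0.5 − b)/0.179 − 1.96).
- b = 0: 2.5 % false non-inferiority; power 80 %.
- b = 0.10: Φ(0.542 − 1.96) = 7.8 %; power Φ(2.229 − 1.96) = 61 %.
- b = 0.10 at 20,000 per arm: 7.0 %; power falls from 70 % to 51 %.

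**5. What the planned tests would show.** At 10 % prevalence and 25,000 per arm, p < 0.05 needs a difference of 1.96 × √(2×0.10×0.90/25,000) = 0.53 points. A 1-point imbalance has z of about 3.6 and would be flagged, but the estimate would stay as it was. An observed imbalance of 0.5 points in each of the five factors, all in one direction, would be non-significant on every test and would still move mortality by about 0.275/2 = 0.14 points.

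**The case against.** The strongest reply is that adjustment is commonly left to a statistical analysis plan, which is not at hand. A reader might infer that the trial decided to leave the mortality difference unadjusted. The protocol does not say so: it calls the difference neither crude nor unadjusted, and it does not rule adjustment out. That stands. What can be said is that the decision rule is written without a covariate, and that the one case-mix step the protocol does state is unsuited to the purpose.

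A reader might also take the planned tests to be the trial's safeguard against confounding. The sentence describes an ordinary comparison of populations and claims no such role. The stated safeguard is the cross-over, and it deserves credit for what step 2 shows it cancels.

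Third, a reader might infer that a bias of a fifth to half the margin is to be expected. No imbalance figure appears in the documents. Oxygen alone needs an imbalance of about 1.1 points at 10 % prevalence to reach a fifth of the margin (0.10/0.093) and about 2.7 points to reach half (0.25/0.093). More than half from 1-point imbalances needs all five factors to move together. The age effect cannot be sized from the protocol at all. The remark "we chose not to include age as a factor in the score" concerns the triage score and says nothing about the analysis.

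Finally, arrival vital signs and oxygen treatment are recorded after the triage model is in force, by staff who know which model it is, and oxygen is a treatment. Adjusting for them in the primary analysis could itself introduce bias. This stands and shapes the fix.

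**Conclusion.** The point holds in a limited form and should be acted on. As written, the verdict rests on a mortality difference with no covariate named, and the only stated case-mix step can neither show adequate similarity nor correct the result. What is exposed is case-mix change that differs by hospital and period, plus a small remainder of shared seasonal change if the hospitals recruit unequally. Stable hospital differences are not exposed.

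The sizes are conditional. They rest on the Table 2 odds ratios, independent factors, an assumed prevalence of 5-15 %, an assumed residual imbalance of 1 point and independent visits. A shift of 0.10 points is one fifth of the margin. It is enough to triple the nominal 2.5 % error rate or to take about 19 percentage points off power. The documents do not show that a shift of that size occurred or is likely.

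**What to change.** In Statistics, before mortality is compared by triage model:
- Make the primary estimate a risk difference standardised for age and sex. Fit a logistic model with triage model, age (flexibly) and sex, average the predicted risks over all patients under each model, and give the difference with a 95 % confidence interval on the absolute scale. Compare it with the same 0.5-point margin.
- Keep the crude difference as a supportive result.
- Add the arrival vital-sign items and oxygen treatment as a sensitivity analysis, with a separate level for minor-injury patients without measurements. Their recording, and the use of oxygen, could differ by triage model.
- Report standardised differences between the populations in place of significance tests.

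Age must be known because eligibility depends on it. That sex is recorded is my assumption. Standardising for age and sex removes only the imbalance those two carry. Severity differences at a given age remain, and the sensitivity analysis is there to show how much they matter.

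The cost is a few sentences and slightly more analysis, with no new patients. Inclusion has already ended, so any departure from the published rule must be documented as made before the unblinded comparison.

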### Timeline

After a 1 week learning period for the staff, the study was initiated the 1st of March, 2015. Herlev Hospital was selected to begin with CTA, i.e. Bispebjerg Hospital continued their use of DEPT triage. This continued until the 17th of August 2015. Subsequently, the hospitals crossed-over. By the end of January 2016 the inclusion

**Table 3** Area under the curve results for the Receiver-Operating Characteristics for DEPT, CTA and a quick clinical assessment in the TRIAGE database

|                     | AUC  | Standard error |
|---------------------|------|----------------|
| CTA                 | 0735 | 0,02           |
| Clinical assessment | 0705 | 0,02           |
| DEPT                | 0605 | 0,02           |

stopped as planned. A total of approximately 50,000 patient visits have been recorded.

### Discussion

Emergency department (ED) triage impacts most patients and it can be a valuable tool for managing a crowded and busy ED. However, existing models of triage are supported by limited evidence. The Copenhagen Triage Algorithm (CTA) aims to be a faster and better way to identify acutely ill patients as well as the less urgent patients in the ED. The CTA Study is a randomized trial comparing CTA to the standard Danish Emergency Process Triage (DEPT) in an unselected population. To the best of our knowledge, this is the first study to prospectively evaluate a triage model in a randomized study. If the hypothesis of non-inferiority in detecting mortality is confirmed CTA will provide less resource consuming method of triage in the ED while still identifying patients in need of urgent care.

The time and resources used on systematic triage is not without a price as crowding in the ED is a well-established risk that can compromise patient safety [1]. Overcrowding in the ED happens when the patient load exceeds the available resources. This situation leads to increased length of stay and mortality across patients both high and low risk [30, 31]. A retrospective study of visits to the Canberra Hospital ED [31] showed that patients presenting to the ED during “overcrowded shifts” had a 34 % higher risk of 10-day in hospital mortality than patients presenting during normal shifts. This risk persisted even when accounting for level of triage (by Australasian Triage Scale) suggesting a level of under-triage during crowded shifts [31]. A systematic review of crowding in the ED [30] found ED bottlenecks to be common in the literature often arising from inadequate staffing. As triage by definition is time and resource consuming, speeding up this process alone could help alleviate some of these problems.

Compared to other triage models CTA is a vastly simpler model comprised of vital signs (blood pressure, heart rate, arterial oxygen saturation, respiratory rate, and the need for oxygen treatment) combined with a clinical assessment by the ED nurse. Since vital signs are measured as part of any patient admission except for minor injuries, the only additional time consuming part

[figure not shown]

of CTA is the clinical assessment which can be done in few minutes even by clinically uneducated staff [25]. This is contrasted by most existing triage models such as ATS, MTS, DEPT and CTAS that use extensive lists of primary complaint or causes of contact [14, 21] aimed at identifying potentially urgent patients. These aim to find the patients primary symptom and triage based on prior consensus of the urgency of symptoms. These are mostly based on expert opinion and has been shown to lead to over-triage, increasing the triage level for about half the patients while lowering the sensitivity and specificity of the final triage [21].

Abnormal vital signs are strong predictors of mortality in patients admitted through ED's [21]. Though smaller studies have shown that vital signs alone are insufficient to detect the critically ill [32, 33], combining these with a clinical assessment by the ED nurse may significantly improve this without using extra resources [25]. Which vital signs and cut-off points should be used is still a subject of debate. In most models, like the ATS, it is established by expert opinion [34] and a systematic review of the literature from 2011 by Farrohknia et al. [15] showed limited or insufficient evidence for any of the vital signs usually used in triage models (respiratory rate, arterial oxygen saturation, heart rate, and level of consciousness). Thus we decided to define new cut-off values based on the large cohort of patients we had gathered.

As the vital signs were meant to reflect acute illness, we chose not to include age as a factor in the score. Biomarkers were not a part of this study though several biomarkers have been shown to be strong predictors of mortality [35, 36]. In the future, a combined score of vital signs and biomarkers may be the most sensitive method of detecting the vast amount of non-urgent patients visiting the hospital every day [24, 37].

